## Abstract

**Background:**

The Extension for Community Health Outcomes (ECHO) Autism Program trains clinicians to screen, diagnose, and care for children with autism spectrum disorder (ASD) in primary care settings. This study will assess the feasibility and impact of integrating an artificial intelligence (AI)–based ASD diagnosis aid (the *device*) into the existing ECHO Autism Screening Tool for Autism in Toddlers and Young Children (STAT) diagnosis model. The prescription-only Software as a Medical Device, designed for use in children aged 18 to 72 months at risk for developmental delay, produces ASD diagnostic recommendations after analyzing behavioral features from 3 distinct inputs: a caregiver questionnaire, 2 short home videos analyzed by trained video analysts, and a health care provider questionnaire. The device is not a stand-alone diagnostic and should be used in conjunction with clinical judgment.

**Objective:**

This study aims to assess the feasibility and impact of integrating an AI-based ASD diagnosis aid into the ECHO Autism STAT diagnosis model. The time from initial ECHO Autism clinician concern to ASD diagnosis is the primary end point. Secondary end points include the time from initial caregiver concern to ASD diagnosis, time from diagnosis to treatment initiation, and clinician and caregiver experience of device use as part of the ASD diagnostic journey.

**Methods:**

Research participants for this prospective observational study will be patients suspected of having ASD (aged 18-72 months) and their caregivers and up to 15 trained ECHO Autism clinicians recruited by the ECHO Autism Communities research team from across rural and suburban areas of the United States. Clinicians will provide routine clinical care and conduct best practice ECHO Autism diagnostic evaluations in addition to prescribing the device. Outcome data will be collected via a combination of electronic questionnaires, reviews of standard clinical care records, and analysis of device outputs. The expected study duration is no more than 12 months. The study was approved by the institutional review board of the University of Missouri-Columbia (institutional review board–assigned project number 2075722).

**Results:**

Participant recruitment began in April 2022. As of June 2022, a total of 41 participants have been enrolled.

**Conclusions:**

This prospective observational study will be the first to evaluate the use of a novel AI-based ASD diagnosis aid as part of a real-world primary care diagnostic pathway. If device integration into primary care proves feasible and efficacious, prolonged delays between the first ASD concern and eventual diagnosis may be reduced. Streamlining primary care ASD diagnosis could potentially reduce the strain on specialty services and allow a greater proportion of children to commence early intervention during a critical neurodevelopmental window.

**Trial Registration:**

ClinicalTrials.gov NCT05223374; https://clinicaltrials.gov/ct2/show/NCT05223374

**International Registered Report Identifier (IRRID):**

PRR1-10.2196/37576

## Introduction

### Background

Autism spectrum disorder (ASD), a neurodevelopmental disorder impacting both communication and behavior, affects approximately 1 in every 44 children in the United States [1]. Targeted early intervention during a critical neurodevelopmental window is recommended to maximize long-term cognitive gains [2,3], adaptive behaviors [4-6], social and emotional functioning [7,8], and verbal fluency [8,9]. ASD evaluations have traditionally been managed in specialist settings; however, a rapid rise in prevalence rates over the past half century [10] has outpaced specialist capacity and led to prolonged wait times for diagnostic evaluations [10-13]. Currently, families in the United States may wait as long as 18 months between initial screening by their primary care clinician and diagnosis by a specialist [11].

Rising ASD prevalence rates, combined with specialist shortages, have contributed to significant diagnostic delays in the United States. Although ASD can be reliably diagnosed at as early as 18 months, the mean age of ASD diagnosis has remained >4 years since the Centers for Disease Control and Prevention began tracking prevalence rates [1,14-16]. The average 3 years delay from first parental concern to eventual diagnosis recorded in the literature is even longer for demographic groups that include girls, children of color, and children who are rural residing or of lower socioeconomic status [17-20]. An estimated 27% of children with ASD in the United States remain undiagnosed at the age of 8 years [20].

Given the importance of early diagnosis and intervention, the American Academy of Pediatrics has recommended that all children be screened in primary care at 18 and 24 months, in addition to whenever caregivers express concern [12]. When they feel confident, upon a failed screen, primary care clinicians are encouraged to make the ASD diagnosis themselves using the Diagnostic and Statistical Manual of Mental Disorders–fifth edition (DSM-5) criteria [12]. Alternatively, they can refer to specialists for further assessment. However, studies suggest that clinicians do not consistently screen or refer to these recommendations [21]. Currently, <1% of all ASD diagnoses are made by primary care clinicians in the United States [21,22].

The low rates of ASD diagnosis in primary care settings may be explained by several factors. Clinician–identified barriers include a lack of ASD-specific training and low self-efficacy in making the diagnosis, as well as time constraints that limit their ability to comprehensively evaluate, review results, and discuss treatment plans with families in primary care [23-26]. Complex presentations in children with ASD, including multiple overlapping comorbidities and a diverse spectrum of symptoms, can also confound the diagnosis [27]. Although diagnostic tools have been developed to support accurate evaluations [28], *gold standard* ASD diagnostic instruments with the highest validity [28-30] are typically poorly suited to use in primary care. This is because they are time intensive and typically require in-person delivery in a clinical facility and specialist training for reliable administration. Even when clinicians receive specialist training, primary care reimbursement rates may be insufficient to justify the effort [31].

### Device Development

Diagnosis aids tailored specifically for use in primary care are urgently needed to streamline ASD evaluations and enhance primary care diagnostic capacity. In response to this need, an artificial intelligence (AI)–based Software as a Medical Device [32] was developed to support health care providers in diagnosing or ruling out ASD in children aged 18 to 72 months with concerns for developmental delay. The device is indicated for use by health care providers who have prescriptive authority in their state of practice. For the purposes of this study the device will be used exclusively by primary care Extension for Community Health Outcomes (ECHO) Autism clinicians. The device was developed using patient record data from thousands of children with diverse conditions, presentations, and comorbidities who were either diagnosed with ASD or confirmed not to have ASD based on standardized diagnostic tools [29,30] and representing both sexes across the supported age range. The underlying device algorithm was iteratively improved, supplemented with ASD expert input, and prospectively validated for over 7 years [33-38]. Key steps involved in device use are illustrated in Figure 1.

**Figure 1 figure1:**
[figure not shown]
Overview of device use. ASD: autism spectrum disorder; HCP: health care provider.

The device integrates 3 independent inputs within its gradient-boosted decision tree algorithm: a brief caregiver questionnaire (completed via a mobile app), a video analyst questionnaire based on the analysis of 2 short home videos uploaded by the caregiver (completed in the video analyst portal), and a health care provider questionnaire (completed in the health care provider portal). The device evaluates inputs based on the predictive features that are most indicative of ASD. If the information provided is sufficiently granular, the device will provide an *ASD Positive* or *ASD Negative* output. When a highly predictive determination cannot be made, the device abstains from providing a result (*No Result* output). Following strong pivotal trial results [39], the device received Food and Drug Administration (FDA) marketing authorization on June 2, 2021 [40]. In a prospective, double-blinded multisite pivotal trial, the device was found to facilitate timely and accurate ASD diagnostic evaluation in nearly a third of the study cohort while minimizing false negatives to maintain clinical safety [39]. However, real-world evidence is needed to learn more about the utility and impact of the device in everyday US primary care settings.

### The ECHO Autism Primary Care Model

ECHO Autism primary care [41,42] is a virtual learning program in which primary care clinicians receive guidance from ASD experts regarding best practices for ASD screening, identification, and management of medical and psychiatric comorbidities. The diagnostic component of the ECHO Autism primary care model involves training clinicians to conduct diagnostic assessments for ASD using the Screening Tool for Autism in Toddlers and Young Children (STAT), a level 2 ASD screener used as a diagnostic observational measure. The ECHO Autism STAT model provides training and mentorship to equip clinicians to diagnose ASD in cases that are clear and unambiguous and appropriately identify and refer complex cases for further assessment [43]. A 12-month pilot study with 18 participating clinicians was conducted using the ECHO Autism STAT model [43]. In this study, participating clinicians presented the results of their assessment to the ECHO Autism expert hub team for specialist input before guiding the diagnostic pathway to include either a diagnosis of ASD or a referral for further specialist evaluation. This pilot study showed that 73% of the participants reported acceptance of referrals for ASD diagnostic evaluations following program completion, and 80% reported an increase in the number of children with ASD in their caseloads. In addition, the pilot demonstrated a 2- to 6-month decrease in time to access services when compared with standard-of-care diagnostic pathways [41]*.*

### Study Objectives

The objective of this study is to assess the feasibility and impact of integrating the device into the existing primary care diagnostic pathway, the *ECHO Autism STAT model*.

## Methods

### Ethics Approval

The study was approved by the institutional review board of the University of Missouri-Columbia (institutional review board–assigned project number 2075722) and registered with ClinicalTrials.gov (NCT05223374).

### Study Design

This prospective observational study was designed to obtain real-world evidence pertaining to the feasibility and impact of integrating the device into a primary care ASD diagnostic pathway. Demographic, clinical, and qualitative user experience data will be obtained from eligible participants. All decisions regarding patient care will be determined by the ECHO Autism clinicians, as the study is noninterventional. All clinical outcomes will be assessed by the ECHO Autism clinician, as in routine clinical practice.

### Study Population

#### ECHO Autism Clinicians

##### Inclusion Criteria

Clinicians eligible for study participation will be practicing primary care physicians and nurse practitioners who are able to evaluate patients for ASD as part of their scope of practice. All clinicians must have received training in the ECHO Autism Communities diagnostic model from the University of Missouri ECHO Autism team before study enrollment.

##### Exclusion Criteria

Clinicians who are unable to evaluate patients with suspected ASD or who have not completed the ECHO Autism diagnostic training will be excluded from study enrollment.

##### ECHO Autism Program Recruitment

Starting in 2016, practicing primary care clinicians located in geographically diverse areas across Missouri were invited to participate in ECHO Autism STAT. Participants were identified through word of mouth, professional association listservs, and strategic recruitment from underserved locations. This program was a continuation of the existing ECHO Autism primary care program that started in 2015. A 2-day training was added focused on use of a direct behavior observation tool (STAT) and comprehensive diagnostic interviewing. The ECHO Autism STAT participants completed in-person training, regularly participated in ECHO Autism telementoring sessions, and achieved reliability with the certified trainer on the STAT observation. After completion of the training elements, these participants were eligible to bring diagnostic cases for discussion during the tele–ECHO Autism sessions. Only clinicians completing all elements of the ECHO Autism diagnostic training are eligible for participation in this study. Eligible clinician participants will be informed of the planned study, offered 2 sessions to ask questions about study participation, and consented through usual research procedures.

#### Patients and Caregivers

##### Inclusion and Exclusion Criteria

At the time of screening, patients must meet all of the inclusion criteria (Textbox 1) to be eligible for study enrollment. Patients who meet any of the exclusion criteria (Textbox 1) will not be eligible for enrollment in the study.

Inclusion and exclusion criteria.
**Inclusion criteria**
Must be aged 18 to 72 monthsMust have developmental delay concerns expressed by caregivers, clinicians, or other community-based professionalsThe participating caregiver must speak English proficiently in the opinion of the clinician.Must be able to read, understand, sign, and date the informed consent formMust have a smartphone using either an iOS or Android operating system (as of June 2022, iOS 14 or 15 and Android 11 or 12, excluding Android Go, are supported; future updates are planned to ensure ongoing compatibility with new operating system versions as they are released)Must be willing to have the child videotaped as part of the device inputMust meet device labeling requirements
**Exclusion criteria**
Participants with a prior diagnosis of autism spectrum disorder rendered by a clinicianParticipants having any other medical, behavioral, or developmental condition that in the opinion of the clinician, may confound study data or assessmentsParticipants whose age on the date of enrollment is outside the target age rangeParticipants who have, to the best of their knowledge, been previously enrolled in any clinical study or survey involving the device or who have a caregiver who has been enrolled in any such studyParticipants whose medical records have been included in any internal device machine learning training or validation sets

##### Patient Recruitment

Participants will be recruited from the population of patients that the ECHO Autism clinician would see as part of their usual enhanced primary care practice. As part of routine practice, ECHO Autism clinicians receive referrals from external primary care clinicians, and when the referrals are received, families will be informed of the opportunity to participate in the study if deemed eligible. Participating clinicians or their designees will inform caregivers of children presenting with a concern for developmental delay about the study. Additional recruitment strategies such as social media, flyers, and email communication with community clinicians may be used as needed to reach recruitment goals.

### Study Flow

#### Overview

This study is being conducted by the University of Missouri ECHO Autism Communities Research Team. Eligible caregivers of patients with a concern for developmental delay and ECHO Autism clinicians will complete the informed consent process before entering the study. Once enrolled, ECHO Autism clinicians will provide routine clinical care and conduct best practice ECHO Autism diagnostic evaluations with the addition of device prescriptions for patients suspected of having ASD. Patients will be followed up with routine clinical care on the schedule shown in Figure 2. Data will be collected at the end of the 3-month follow-up period. The clinician will complete a visit form for any interim visits that occur between visit 1 and the 3-month follow-up appointment.

The study flow is summarized in Figure 2 and described in detail in the following sections.

**Figure 2 figure2:**
[figure not shown]
Study flow. ASD: autism spectrum disorder; ECHO: Extension for Community Health Outcomes; HCP: health care provider.

#### Visit 1: Eligibility Determination

An appointment is scheduled for a participant (patient) with concern for developmental delay and their caregiver. During the first clinic visit, the ECHO Autism clinician will observe the participant and conduct a DSM-5 interview to determine whether the participant requires further ASD evaluation.

#### Baseline Data Collection

The ECHO Autism clinician will connect the caregiver of any potential participant requiring further evaluation for ASD to the University of Missouri ECHO Autism Communities research team. Before visit 1, the research team will obtain consent from the family. The research team will provide instructions on how to complete the electronic study baseline caregiver questionnaires and download the device’s caregiver app. The research team will also send electronic baseline ECHO Autism clinician questionnaires to the clinician to complete. The clinician will prescribe the device.

#### Device Completion

Once the device is prescribed by the clinician, the study sponsor will release the access code to the study team, who will then email it to the caregiver. The caregiver will download the mobile app to their smartphone and access the app using the code. The caregiver will then complete an 18- or 21-item age-dependent caregiver questionnaire (*device input 1*) and record and upload two 1.5-minute to 5-minute videos of the child on the mobile app. The uploaded videos will be remotely reviewed and scored on a 28- or 33-item video analyst questionnaire (*device input 2*) by a trained video analyst via the video analyst portal*.* The ECHO Autism clinician then has the option to *either* complete the health care provider questionnaire, which is a 13- or 15-item age-dependent questionnaire (*device input 3*), themselves or schedule the participant for a telehealth provider appointment, during which the questionnaire will be completed by the telehealth provider. The device algorithm then analyzes all 3 inputs and produces either a *positive ASD*, *negative ASD*, or *indeterminate/no result* output for the clinician to review.

#### Visit 2: Diagnostic Results Meeting

After the device output is received, the clinician will synthesize their diagnostic impressions (ie, in-person observation, DSM-5 interview, and questionnaires) and the device output to determine whether the participant meets the criteria for a diagnosis of ASD. The clinician may also request access to view the participant’s videos when making a diagnosis. In cases where the clinician’s judgment conflicts with the device output, the diagnostic determination of the clinician (who remains the decision-maker in the diagnostic process) takes precedence. This is consistent with the device’s FDA market authorization status as a diagnosis aid intended to support health care providers in diagnosing ASD rather than as a stand-alone diagnostic device.

For participants whom the clinician determines as meeting the criteria of ASD, the clinician will deliver the diagnosis to the caregiver during visit 2. In addition, the clinician will schedule a 3-month follow-up visit. The research team will then send electronic postdiagnostic questionnaires to the caregiver and the clinician to be completed 1 to 3 (up to 10) days after visit 2.

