#### Visit 3: Treatment Progress Meeting

The clinician will follow-up with the caregiver for 3 months (+21 or –21 days) after the participant receives an ASD diagnosis to discuss treatment progress and screen for any other medical and psychiatric comorbidities. The research team will send electronic postdiagnostic questionnaires to the caregiver and clinician to complete 1 to 3 (up to 10) days after this follow-up visit.

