**Data collected for secondary objectives**
Patient outcomes correlating with time to initiating therapy following a positive autism spectrum disorder (ASD) diagnosisDistance from patient home to nearest ASD specialist centerLevel of clinician self-efficacy in using the device as part of the evaluation and diagnosis of children with suspected ASDQualitative data on the following: caregiver satisfaction with the diagnostic process; time from caregiver concern to diagnosis; clinician certainty rating for diagnostic determination; clinician satisfaction with using the device as part of the Extension for Community Health Outcomes (ECHO) Autism diagnostic process; caregiver perception of the device with validated questionnaire; determination of whether the use of the device enhances the efficiency and feasibility of the ECHO Autism Communities diagnostic process; likelihood to recommend (clinician and caregiver); efficiency and feasibility of ECHO Autism Community–based diagnostic process, as measured by self-efficacy, certainty ratings, perceived barriers, and practice patterns questionnaires; percentage of positive outcomes correlating with shorter durations between diagnosis and treatment; percentage of caregivers who feel they received a high-quality evaluation; percentage of clinicians with increased self-efficacy in using the device as part of the diagnostic process; percentage of clinicians finding the device helpful in the diagnostic process; percentage of positive device perceptions from caregiver; barriers to app use for caregivers; clinician-perceived barriers to practice implementation of deviceAssessment of insurance coverage or reimbursement (although insurance will not be billed for this study)Amount of time required for clinicians to make a diagnosisPercentage of clinician participants reporting a positive change in practice flow because of using the device as part of their diagnostic processPercentage of patients for whom the device can provide a determinate result (ASD positive or negative)Summary of interventional treatments recommended by the clinician following diagnosisChanges in clinician clinical practice flowChange in quality of life measuresTime associated with device use

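### As written, the questionnaires after visit 2 and the 3-month visit are described only for children diagnosed with ASD, while the caregiver outcomes and the general follow-up text carry no such limit

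*Protocol article*

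**What the plan says.** **Visit 2: Diagnostic Results Meeting.** The first paragraph covers how the clinician decides whether ASD criteria are met. The second opens "For participants whom the clinician determines as meeting the criteria of ASD, the clinician will deliver the diagnosis to the caregiver during visit 2". It continues "In addition, the clinician will schedule a 3-month follow-up visit" and then "The research team will then send electronic postdiagnostic questionnaires to the caregiver and the clinician to be completed 1 to 3 (up to 10) days", counted from visit 2. The section describes no steps for a child found not to have ASD, left unresolved or referred on.

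**Visit 3: Treatment Progress Meeting.** The visit falls 3 months (plus or minus 21 days) "after the participant receives an ASD diagnosis to discuss treatment progress and screen for any other medical and psychiatric comorbidities". The second set of questionnaires is timed from this visit.

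**Sections that read more broadly.** Study Flow: Overview says patients are followed on the schedule in Figure 2 and adds "Data will be collected at the end of the 3-month follow-up period". Study Duration runs patient participation through the 3-month visit. Diagnostic Procedures refers to follow-up once diagnostic results have been given, whatever they are. None of the three mentions an ASD diagnosis as a condition.

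**Outcomes.** Textbox 2 lists the "percentage of caregivers who feel they received a high-quality evaluation", positive caregiver perceptions of the device, likelihood to recommend (clinician and caregiver), barriers to app use, and clinician certainty about the diagnostic determination. None is restricted to diagnosed children. Sample Size defines the patient group by eligibility for an ASD evaluation, not by its result.

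**The concern.** Families who do not receive an ASD diagnosis complete the same app questionnaire and home videos as those who do. Device Completion foresees negative and no-result outputs, and the description of the ECHO Autism model says complex cases are referred on, so such families are to be expected. Their view of the evaluation and of the device may differ from that of families who leave with a diagnosis.

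If they are not surveyed, a percentage labelled as one of caregivers becomes a percentage of caregivers whose child was diagnosed. Any difference in opinion between the two groups then passes into the reported result and cannot be seen in the data. Strengths and Limitations discusses selection into the study and attrition from it, but not this conditioning on the diagnosis. The Discussion expects the study to inform on acceptability to families, so the point bears on a stated aim.

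**Working it through.** **Step 1: who receives each instrument, on the text.**

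| Item | Condition in the text |
|---|---|
| Questionnaires after visit 2 (caregiver, clinician) | No ASD condition in the sentence itself; timed from visit 2; stands third in a paragraph opened by children meeting ASD criteria |
| 3-month visit | Explicitly timed from an ASD diagnosis |
| Questionnaires after the 3-month visit | Timed from that visit, so also tied to an ASD diagnosis |
| Data at the end of 3 months (Overview) | None |
| Participation through the 3-month visit (Study Duration) | None |
| Follow-up in Diagnostic Procedures | Diagnostic results of any kind |
| Clinician postproject survey (Textbox 3) | Not tied to a child's diagnosis |

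For a child without an ASD diagnosis, the general sections give a 3-month end point, but the Visit 3 section gives no date from which to count it. For the questionnaires after visit 2, the restriction follows from the order of the sentences: the scheduling sentence is an addition to delivering the diagnosis, and the questionnaire sentence comes next in that sequence. That is the natural reading, but it is an inference.

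**Step 2: size.** The article states no diagnosis rate, no satisfaction rate and no precision target, so there is no figure to reproduce. Let q be the share of evaluated children without an ASD diagnosis, and s1 and s0 the favourable percentages in diagnosed and undiagnosed families.

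- All-family percentage = (1 − q) × s1 + q × s0
- Percentage if only diagnosed families are surveyed = s1
- Overstatement = s1 − [(1 − q) × s1 + q × s0] = q × (s1 − s0)
- 95% half-width = 1.96 × sqrt(p(1 − p)/n)

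Inputs: N = 100 is the article's maximum. Assumed: s1 = 85%; q = 20%, 35%, 50%; s1 − s0 = 10, 20, 30 points; full response among those surveyed.

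| q | Respondents | Overstatement for a gap of 10 / 20 / 30 points | Half-width at p = 85% |
|---|---|---|---|
| 20% | 80 | 2 / 4 / 6 | 7.8 |
| 35% | 65 | 3.5 / 7 / 10.5 | 8.7 |
| 50% | 50 | 5 / 10 / 15 | 9.9 |

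Example: q = 35% and a gap of 20 points give 0.65 × 85 + 0.35 × 65 = 78%, against 85% reported, a difference of 7 points. With all 100 families surveyed, the half-width at p = 85% is 1.96 × sqrt(0.85 × 0.15/100) = 7.0 points.

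The overstatement does not depend on s1, only on q and the gap. If undiagnosed families were the more favourable group, its sign would reverse.

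**The case against.** A reader might infer that the plan excludes every family with a negative or unresolved evaluation, and that all satisfaction and recommendation results are affected. The article does not support that.

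- The questionnaire sentence has no ASD condition of its own and is timed from visit 2.
- The Overview, Study Duration and Diagnostic Procedures sections are not limited to diagnosed children.
- The schedule is in Figure 2, which is not available here and may show a route for the other children. The full protocol may also give one.
- Clinician satisfaction, self-efficacy and perceived barriers come from surveys before and after the project, which do not depend on any child's diagnosis. Likelihood to recommend has a clinician part as well as a caregiver part.
- Timing a treatment-progress visit from an ASD diagnosis is reasonable in itself.
- The illustrative percentages are assumed.

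All of this stands, and it limits the point to what the text describes. It does not remove the point. The broader sections conflict with the timing of visit 3 and do not explain it. Nor does the text anywhere say that a caregiver of a child without an ASD diagnosis receives the survey after visit 2. Someone following the visit sections as they stand would not send it.

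A further inference would be that a missed later diagnosis goes unseen and that this is the chief harm at stake. The article does not support this either: interim visit forms and the general follow-up text apply to all participants, and the document does not rank harms in this way.

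**Conclusion.** The point holds as a conflict within the text that, if the visit sections are followed, conditions the caregiver percentages and the per-child clinician questionnaires on a positive diagnosis. The timing of visit 3 and its questionnaires is explicit; the restriction of the questionnaires after visit 2 is the natural reading but is not stated.

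The likely effect is to overstate acceptability, by about 2 to 15 points, with 50 to 80 respondents in place of 100. This rests on assumed values for the undiagnosed share (20% to 50%) and for how much less favourable their families are (10 to 30 points). The document fixes neither value, nor the direction of the gap. Results from the clinician postproject survey are unaffected. The change is worth making because it is cheap and the missing responses could not be recovered at analysis.

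**What to change.** 1. Reconcile Study Flow: Overview, Visit 2, Visit 3, Study Duration and Diagnostic Procedures, so that it is clear which steps apply to every evaluated participant and which only after an ASD diagnosis.
2. Send the existing electronic post-visit-2 caregiver and clinician questionnaires to every evaluated participant, in the same window of 1 to 3 (up to 10) days after the results meeting or the decision to refer, whatever the diagnosis or device output.
3. Report each caregiver percentage with its denominator, overall and by diagnostic outcome (ASD, not ASD, unresolved or referred).

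The cost is a change of wording and a few more survey invitations; no new instrument is needed. Checking routine records at about 3 months for later ASD diagnoses among the other children would add an outcome. It is optional and not part of this fix.
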